### Potential interpretations of prespecified group comparisons

The proposed design provides the opportunity to make a number of meaningful comparisons. First, the contrast between the SAR and BI-B groups allows a determination of the incremental benefit of the assessment + BI + booster sessions over and above the effects of the assessment alone. This contrast has been conducted in most prior SBIRT studies and is the one for which the group differences and effect size may be attenuated due to potential assessment reactivity. The second comparison, between the SAR and MSO, allows the determination of any incremental therapeutic effects of assessment over and above minimal contact. This comparison provides the quantification of the assessment reactivity effect. The final comparison, between the BI-B and MSO groups, provides a measure of the total effect of the intervention, including any therapeutic effects of assessment and referral. The MSO condition actually offers a better approximation of true treatment-as-usual, as opposed to SAR, since the latter condition represents a greater intensity of intervention than is typically found in EDs.

There are many potential equalities and inequalities that can hold between the three arms of the SMART-ED design. Assuming that abstinence is the outcome (and the bigger the better), the most intuitive results of possible comparisons and appropriate conclusions are depicted in Table 1. For example, if MSO < SAR < BI-B, we may conclude that there is both assessment reactivity and a treatment effect. Other rows can be interpreted similarly. Thus, each significant difference, or lack of difference, between groups would provide meaningful evidence of the presence or absence of assessment and/or treatment effects but with different implications for practice.

**Table 1 T1:** Interpretation of potential assessment and treatment effects based on outcomes of contrasts among SMART-ED conditions

**Equalities and Inequalities**					**Conclusions**	
MSO^*^		SAR**		SAR/BI-B†	Assessment Reactivity	Treatment Effects
	<		<		Yes	Yes
	<		=		Yes	No
	=		<		No	Yes
	=		=		No	No

*MSO = minimal screen only. **SAR = screening, assessment, and referral to treatment if indicated or requested. †SAR/BI-B = screening, assessment, and referral if indicated or requested plus brief intervention and subsequent telephone follow-up booster sessions.

While assessment has typically been an integral component of BI, in a number of general health-care settings it is likely that BI may be conducted without assessment; there is often limited or no time for conducting an assessment beyond a brief screen in such settings, and assessment is often seen as complex by generalist clinicians. The possibility and effectiveness of conducting BIs without assessment is a condition that is not examined in the current design. Conversely, it is possible to have assessment without treatment. If the SAR condition has a better outcome than the minimal screen only (MSO) condition, and the BI-B condition does not outperform SAR, then a case could be made for simply conducting an assessment and subsequent referral to specialty substance abuse treatment. Given the added costs involved, an intervention should be avoided if it does not significantly add to the outcome over and above that of SAR.

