**Methods/design:**

The protocol employs a 3-arm design. Following an initial brief screening, individuals identified as positive cases are consented, asked to provide demographic and locator information, and randomly assigned to one of the three conditions: minimal screening only, screening + assessment, or screening + assessment + brief intervention. In a two-stage process, the randomization procedure first reveals whether or not the participant will be in the minimal-screening-only condition. Participants in the other two groups receive a more extensive baseline assessment before it is revealed whether they have been randomized to also receive a brief intervention. Comparing the screening only and screening + assessment conditions will allow determination of the incremental effect of assessment reactivity.

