## Methods/design

### Overview

These concerns were taken into consideration in the design of the NIDA Clinical Trials Network’s protocol, Screening, Motivational Assessment, Referral, and Treatment in Emergency Departments (SMART-ED) [26]. The study, which is being conducted in six emergency departments across the US, is evaluating the efficacy of a motivational interviewing-based BI delivered in the ED setting, targeting individuals who screen positive for using/abusing illicit drugs or prescription medications. All study materials and procedures have been reviewed and approved by the appropriate Institutional Review Boards (IRBs) of participating universities and affiliated EDs. The trial will be conducted in compliance with protocol, International Conference on Harmonisation Good Clinical Practice guidelines, and applicable regulatory requirements. An independent Data and Safety Monitoring Board oversees the study.

In order to assess the independent contributions of assessment and the BI to outcomes in the study population, a three-arm design was adopted. The three treatment groups are (1) a minimal screen-only condition (MSO) in which participants receive as little interaction as possible and do not complete an intensive baseline assessment; (2) screening, assessment, and (if indicated or requested) referral to treatment (SAR); and (3) screening, assessment, and (if indicated or requested) referral, plus BI lasting up to 30 minutes in the ED followed by two telephone booster intervention sessions within 1–4 weeks following the ED visit (BI-B). Figure 2 presents an overview of this design.

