#### Screening and referral (SAR)

Participants in the SAR group will receive the same informational pamphlet as the MSO group. Those with probable dependence (NM-ASSIST score ≥27 for any drug or alcohol) will also be provided with minimal scripted feedback to let them know their score is in the high-risk range, and will receive a recommendation to seek treatment. The RA will provide these participants with an information sheet listing treatment and self-help resources in their community. The latter will be standardized in format but will include site-specific information, i.e., names, addresses, and phone numbers of local addiction treatment agencies in the normal clinical referral network of the participating EDs. Based on our initial site survey, the majority of responding EDs are not currently screening or referring systematically, so the SAR condition represents a level of care significantly higher than treatment-as-usual.

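### SAR versus MSO estimates assessment plus indicated feedback and referral, so MSO < SAR does not by itself establish assessment reactivity

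*Protocol article*

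**What the plan says.** The Abstract (Methods/design) states: "Comparing the screening only and screening + assessment conditions will allow determination of the incremental effect of assessment reactivity". The section *Potential interpretations of prespecified group comparisons* says of SAR versus MSO: "This comparison provides the quantification of the assessment reactivity effect". Table 1 turns this into a rule: both rows with MSO < SAR carry a Yes in the *Assessment Reactivity* column. The Discussion repeats that the design determines what the assessment process contributes.

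The arm descriptions are wider than this label. Under *Screening and referral (SAR)*: "Those with probable dependence (NM-ASSIST score ≥27 for any drug or alcohol) will also be provided with minimal scripted feedback". The same participants "will receive a recommendation to seek treatment", and "The RA will provide these participants with an information sheet listing treatment and self-help resources in their community". The Overview and the Table 1 footnote define SAR as including referral where indicated or requested. Under *Minimal screening only (MSO)*, participants get the informational pamphlet and nothing more. SAR participants get the same pamphlet.

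For BI-B versus MSO, the interpretation section does name the wider content: that contrast measures the total effect, "including any therapeutic effects of assessment and referral".

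**The concern.** The Background defines assessment reactivity as change set off by assessment itself when not even a minimal intervention is given. SAR participants who are told that their score is high-risk, advised to seek treatment and handed a list of services do not meet that condition. The interpretation section allows that referral may be therapeutic when it describes BI-B versus MSO, but leaves referral out when it describes SAR versus MSO.

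SAR versus MSO is one of the three primary contrasts, and separating assessment from intervention is the stated purpose of the design. Suppose advice and referral help and assessment alone does nothing. In the second row of Table 1 (MSO < SAR, SAR = BI-B) that benefit would be entered as reactivity, with nothing entered under treatment. The trial would then report a methodological bias that its comparison cannot separate from a simple clinical service. The limitations in the Discussion cover screening, consent, hair sampling and blinding to study purpose, but not this.

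**Working it through.** **Step 1. What differs between the arms.**

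| Component | MSO | SAR | BI-B |
|---|---|---|---|
| Screening, consent, hair sample | yes | yes | yes |
| Pamphlet | yes | yes | yes |
| Baseline assessment (about 30 minutes) | no | yes | yes |
| High-risk feedback, advice, resource list | no | if NM-ASSIST ≥27 | as in SAR |
| Referral on request | no | yes | yes |
| BI and up to two booster calls | no | no | yes |

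The pamphlet is common to all arms and cancels. SAR versus MSO differs in assessment and in indicated feedback/referral. BI-B versus SAR does not differ in referral content, because BI-B is described as receiving the same information and referral as SAR.

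**Step 2. Decomposition.** Let A be the mean reduction in days of use from assessment alone, q the share of SAR participants who receive feedback/referral, and d its further effect in them. Then

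MSO mean − SAR mean = A + q × d.

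The rule in Table 1 reads this as A. If d > 0, the contrast overstates reactivity by q × d. If d = 0, the label is harmless. If d < 0, it understates reactivity. A larger sample does not change q × d.

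**Step 3. The plan's own sample size.** Inputs from *Sample size determination*: difference 3 days, SD 11, two-sided α = .05/3 = .0167, power 90%, attrition 15%.

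- n per arm = 2 × [11 × (2.394 + 1.282)/3]² = 363.3, so 364 evaluable.
- 364/.85 = 428.2, so 429 per arm. 3 × 364/.85 = 1284.7, so 1285 in total.

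The stated figures reproduce and are not in dispute.

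**Step 4. Illustration of scale.** The article gives neither q nor d, so every value of them below is an assumption. Evaluable per arm: 429 × .85 = 364.65. SE of a difference = 11 × √(2/364.65) = 0.815 days. The smallest significant difference is 2.394 × 0.815 = 1.95 days at .05/3, and 1.96 × 0.815 = 1.60 days at .05. With A = 0, the chance that SAR and MSO differ significantly is:

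| q | d (days) | q × d | at .05/3 | at .05 |
|---|---|---|---|---|
| .25 | 2 | 0.50 | 3.9% | 9.4% |
| .50 | 2 | 1.00 | 12% | 23% |
| .50 | 3 | 1.50 | 29% | 45% |
| .75 | 3 | 2.25 | 64% | 79% |

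The nominal rates are 1.7% and 5%. A value of d = 3 is already demanding: it asks a scripted message and an information sheet to produce the difference the trial was sized to detect between BI-B and SAR. The table shows only that the answer depends on q and d.

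**Step 5. Can the trial's data separate A from q × d?** Not directly. SAR participants below NM-ASSIST 27 who ask for no referral receive assessment only, but MSO has no baseline NM-ASSIST, so they have no randomised counterpart. DAST-10 and AUDIT-C are measured in every arm before randomisation and are stratification factors (cut-offs ≥8 and ≥4). They predict referral only approximately.

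**The case against.** The strongest reply is that the reader is not misled about what SAR contains. The Overview and the Table 1 footnote name referral, and the closing paragraph of the interpretation section reads SAR better than MSO, with no added BI-B benefit, as a case for assessment and referral together. The primary hypotheses and analyses compare days of use and do not mention reactivity. Feedback is scripted, minimal and limited to a subset. All of this stands. It confines the problem to the reading of one contrast but does not repair that reading: the conclusion column of Table 1 and the two interpretive sentences still name assessment alone.

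Some stronger readings are tempting, and the article does not support them.

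- *SAR versus MSO is an invalid comparison.* It is not. Randomisation is intact and the contrast estimates the combined package without bias.
- *The whole SAR arm fails the Background's definition.* Only participants who receive feedback or referral do.
- *The article's remark that SAR exceeds usual care shows that referral works.* The reason given there is that most responding EDs do not systematically screen or refer. Screening is also given to MSO, and the remark makes no claim of efficacy.
- *The bias could equal the full 3-day target.* That needs assumed values, such as 60% referred with a 5-day effect (.60 × 5 = 3.0). Nothing in the article supports either figure.
- *Reactivity may be claimed only if it appears where referral is unlikely.* Less severe patients may respond differently to assessment, so a null result there could reflect effect modification. The trial was also not sized for that subset.

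**Conclusion.** The concern holds as a fault of attribution. SAR versus MSO validly estimates assessment plus indicated feedback/referral, and an MSO < SAR result does not by itself establish assessment reactivity. The fault is mainly one-sided: if feedback and referral do no harm, MSO = SAR remains evidence against reactivity within the precision of the contrast. BI-B versus SAR is not affected in this way, and BI-B versus MSO is already described as a total effect.

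The overstatement is q × d, and neither factor is in the article, so no size can be asserted. The conclusion does not depend on the illustration. It rests on the arm descriptions, the Background's definition and the rule in Table 1. Because the article states that rule itself, this is not a detail left to an analysis plan.

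**What to change.** 1. Relabel the SAR versus MSO contrast as *assessment plus indicated feedback/referral* in the Abstract, in the interpretation section and in the *Assessment Reactivity* column of Table 1. Align the matching sentence in the Discussion.
2. Add to the limitations that the effect of assessment alone is not separately identified, because participants with NM-ASSIST ≥27 in SAR also receive feedback, advice and a resource list, and referral may be requested.
3. Optionally, pre-state SAR versus MSO among participants with DAST-10 < 8 and AUDIT-C < 4 as a supportive, approximate analysis. Do not make the reactivity claim conditional on it.

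Items 1 and 2 cost only wording and a narrower headline claim. They change no arm, test or sample size. Item 3 uses data already collected and sits close to the planned secondary analysis of baseline severity by treatment. It has three drawbacks:

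- **Precision.** The subset's share is not given. If it were 50% or 25% of participants (assumed), the SE would rise from 0.815 to 0.815/√.50 = 1.15 or 0.815/√.25 = 1.63 days.
- **Remaining referral.** Low screening scores do not rule out NM-ASSIST ≥27, which counts alcohol as well as drugs, or a request for referral.
- **Effect modification.** The effect of assessment may itself vary with severity.

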Subsequent attention shifted from post-treatment follow-up assessment to the potential impact of assessments that take place prior to the initiation of treatment in clinical trials [19,20]. These studies found that reductions in drinking/drug use occurred between an initial screening, subsequent intake assessment, and the first therapy session. Further, these screening/post-assessment/pretreatment reductions predicted better treatment outcomes. As an example, Epstein and colleagues [19] found significant reductions in percentage of drinking days after each of the following events: a brief 10-minute telephone screening, a 90-minute clinical screening, and a 3–4 hour baseline research interview. However, there were no changes from baseline to the day before treatment or from the day before treatment to the end of the first week of treatment. Thus, the primary change in drinking behavior occurred prior to treatment initiation. While it could be argued that the observed changes reflected regression toward the mean [21], the increased attention to drinking may initiate a change process and may reflect an active therapeutic benefit of assessment [9,22]. Randomized experimental evaluations of the effects of assessment on measures of alcohol consumption among heavy-drinking college students involved in BIs have similarly found a reactivity effect [10,12,14], supporting the view that an active therapeutic process is at play rather than regression to the mean.

In contrast, studies in EDs targeting alcohol use [23,24] and marijuana [25] have not found an assessment reactivity effect. As an example, ED patients identified as having hazardous drinking patterns were randomly assigned to a screen-only, an assessment-only, or an assessment + intervention condition [23]. Drinking outcomes at a 12-month follow-up indicated that patients in both the screen-only and assessment + intervention conditions had greater, but nonsignificant, improvements compared with those in the assessment-only condition. In a study with a similar design, reductions in drinking-related outcomes were found at a 12-month follow-up among individuals identified as hazardous drinkers in the ED [24]. There were no differences, however, between patients who had been randomized to a 10–15 minute BI, a screen + assessment condition, or a screen-only group.

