### Sample size determination

There is no straightforward way to estimate the effect size of the proposed contrasts across the three conditions due to differences across critical aspects of prior SBIRT studies (e.g., primary care setting rather than ED, or alcohol versus drug use as the primary outcome). While previously published studies guided our estimates of treatment effect, the power analysis and sample size calculations were based on the minimum clinically significant nonstandardized effect that we wish to be able to detect between SAR and BI-B, and estimates of error variance based on the data collected in the Washington State implementation of an SBIRT model in ED setting [48,56]. In order to detect an absolute difference of three days between the two groups, which was considered to be a clinically meaningful difference, and with an estimated standard deviation of 11 days, an anticipated 15% attrition rate, and a Type I error *α* = .05/3 (two-tailed), a total of 1285 subjects (429 in each arm) was determined necessary to have 90% power. Estimating conservatively that 5% of screened patients will meet inclusion criteria, and that 75% of these will consent to participate in the study, it will be necessary to screen 34,267 patients (5711 per site) to achieve the proposed sample of 1285 randomized participants. We propose to screen approximately 160 individuals per week per site to achieve the targeted enrollment rate of six participants per week per site. This will allow recruitment at each site to be accomplished within nine months.

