### Statistical methods for primary analyses

The primary analyses will consist of three prespecified pair-wise comparisons between the MSO, SAR, and BI-B conditions with respect to the primary outcome variable (number of days of use of the primary drug of abuse in the past 30 days at three-month follow-up based on the TLFB), all of which will use a simple closed testing procedure to control family-wide Type I error at no more than 0.05. Linear mixed-model analyses with a random site effect and fixed treatment effect and intercept will be used. These analyses will take into account possible variability in the overall level of abstinence between the sites, possible site-by-treatment interaction, and the level of a baseline covariate (days of use of the primary drug of abuse, as defined at screening by the DAST-10, during the 30 days preceding the baseline assessment). The primary outcome will be analyzed according to the intent-to-treat principle. Patients who refuse treatment will still be followed for outcome in their assigned group, but no attempt will be made to impute outcomes for these patients.

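### Table 1 reads a non-significant contrast as 'No' effect and has no entry for BI-B vs MSO, so effects below the 3-day design value can be called absent even when the total effect is significant

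*Protocol article*

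**What the plan says.** All places are in the protocol article.

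- **Statistical methods for primary analyses:** "The primary analyses will consist of three prespecified pair-wise comparisons between the MSO, SAR, and BI-B conditions", "all of which will use a simple closed testing procedure to control family-wide Type I error at no more than 0.05". These are tests for a difference.
- **Potential interpretations of prespecified group comparisons, Table 1:** two relations are shown, MSO to SAR and SAR to BI-B. Under the heading 'Conclusions', '<' gives 'Yes' and '=' gives 'No', for assessment reactivity and for treatment effects respectively. There are four rows. None shows SAR worse than MSO, and there is no column for BI-B vs MSO.
- **Same section, sentence before Table 1:** "each significant difference, or lack of difference, between groups would provide meaningful evidence of the presence or absence of assessment and/or treatment effects". Here a lack of difference is set against a significant difference, which tells the reader how '=' will be decided.
- **Same section, last paragraph:** "an intervention should be avoided if it does not significantly add to the outcome over and above that of SAR".
- **Same section, first paragraph:** BI-B vs MSO is named and read as the total effect of the intervention, including assessment and referral.
- **Sample size determination:** "In order to detect an absolute difference of three days between the two groups, which was considered to be a clinically meaningful difference". The sizing is for SAR vs BI-B. No expected SAR vs MSO effect is given.

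**The concern.** A non-significant difference test shows that an effect was not demonstrated. It does not show that the effect is absent. That needs a margin and an interval lying inside it, and the article attaches neither to Table 1. The distinction matters here because the design exists to establish whether assessment reactivity occurs, and 'No' in that column would be read as the answer.

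There is also a gap in logic. As true relations, MSO = SAR and SAR = BI-B imply MSO = BI-B. As test outcomes they do not: two steps can each miss significance while their sum reaches it. Because Table 1 has no place for BI-B vs MSO, it can print 'No/No' in a trial whose first-listed primary hypothesis has been confirmed.

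Finally, the sample size is calculated with two-tailed tests, and Background reports an earlier emergency department trial in which "patients in both the screen-only and assessment + intervention conditions had greater, but nonsignificant, improvements compared with those in the assessment-only condition". The table does not say what would be concluded if SAR came out worse than MSO.

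**Working it through.** **Inputs (Sample size determination):** difference 3 days, SD 11, two-sided alpha .05/3, power 90%, attrition 15%. Allocation is 1:1:1 (Randomization procedure).

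**Step 1. Reproduce the stated size** ("a total of 1285 subjects (429 in each arm) was determined necessary to have 90% power").
n per arm = 2 × [11 × (2.394 + 1.282) / 3]² = 363.3, so 364 completers. 364 / 0.85 = 428.2, so 429 per arm. 3 × 429 = 1287, or 1282 without rounding, against 1285 stated. The figure reproduces.

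**Step 2. Precision of one contrast.**
SE = 11 × √(2/364) = 0.815 day. CI half-width = 1.960 × 0.815 = 1.60 days (95%) or 2.394 × 0.815 = 1.95 days (98.33%, matching .05/3). An estimate just short of significance has an upper limit of about twice the half-width, 3.2 to 3.9 days. That is above the 3 days the protocol calls meaningful, yet the table entry would be 'No'.

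**Step 3. Chance of 'No' on one contrast when the effect is real.**
P(not significant) = Φ(z − δ/SE), with z = 1.960 (alpha .05, the pairwise level in closed testing) or 2.394 (.05/3).

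| True difference | alpha .05 | alpha .05/3 |
|---|---|---|
| 3 days | 4% | 10% |
| 2 days | 31% | 48% |
| 1.5 days | 55% | 71% |
| 1 day | 77% | 88% |

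The overall test that comes first in a closed procedure can raise the left column slightly. With all 3 days in the MSO-to-SAR step, the simulation below gives 5% instead of 4%.

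**Step 4. Table 1 outcome against BI-B vs MSO.**
One million simulated trials of three normal means were run, with 365 per arm and SD 11. They were scored by closed testing (2-df overall test at .05, then each pair at .05) and with every contrast at .05/3. The splits are illustrative.

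| True 3-day total, split as | BI-B vs MSO significant | 'No/No' | 'No/No' with BI-B vs MSO significant |
|---|---|---|---|
| 1.5 + 1.5 | 92% / 90% | 22% / 45% | 14% / 36% |
| 1 + 2 | 92% / 90% | 19% / 38% | 12% / 30% |
| 3 + 0 | 95% / 90% | 4% / 9% | 2% / 6% |

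(First figure closed testing, second .05/3.) Replacing the overall test by a Bonferroni one moves results by about 2 points at most.

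**Step 5. What a 3-day CI rule would do.**
The CI lies within ±3 days when the estimate lies within ±(3 − 1.60) = ±1.40 (95%) or ±(3 − 1.95) = ±1.05 (98.33%).
- True difference 0: 2Φ(1.40/0.815) − 1 = 91%, or 2Φ(1.05/0.815) − 1 = 80%. A genuine null can usually be reported as excluding 3 days.
- True difference 2 days: Φ((1.40 − 2)/0.815) = 23%, or Φ((1.05 − 2)/0.815) = 12%.

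So at 2 days and the 95% level, 23 of the 31 points of non-significance would still satisfy the rule. Excluding 3 days must therefore not be worded as no effect.

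**The case against.** The best defence is that Table 1 illustrates and does not decide. The section concerns potential interpretations, says that many patterns can arise, and offers the table as the most intuitive ones. No test, alpha, endpoint or sample size depends on it. This stands as a limit on severity. It does not remove the fault, because the same text calls the entries appropriate conclusions, they are flat Yes/No, and "an intervention should be avoided if it does not significantly add to the outcome over and above that of SAR" carries no hedge.

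A reader might infer that the article leaves BI-B vs MSO uninterpreted. It does not: the first paragraph of the section says what that contrast measures. The omission is confined to the table and the reading built on it.

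A reader might also infer that the trial would often miss the effect it was built to find. The figures do not support that: at 3 days the false 'No' rate is 4–10%. The high rates belong to effects below the protocol's own minimum meaningful difference. Even so, 'No' is stronger than 'less than 3 days', and a smaller reactivity effect can still attenuate the SAR vs BI-B contrast.

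Three further points stand in part. The upper figures use the planning alpha, and closed testing puts the planned analysis nearer the lower ones. The baseline covariate could reduce the SE, while site-by-treatment variability could act the other way. And the sentence on avoiding an intervention appeals to cost, so it can be read as placing the burden of proof on the add-on. That reading is legitimate but should be stated, because beside a table that says 'No' it will be taken as a finding of no benefit.

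**Conclusion.** The point holds for Table 1, the sentence introducing its reading, and the advice at the end of the section. Non-significance is turned into absence with no margin, and the table can contradict a significant primary contrast. For one contrast the false 'No' rate is 4–10% at 3 days, 31–48% at 2 days and 55–71% at 1.5 days. 'No/No' beside a significant total effect has a probability of about 14–36% for an even split of 3 days and 2–6% if the effect sits in one step.

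These figures assume SD 11 in every arm, normal means, 15% attrition, no covariate gain and no site-by-treatment variance. The splits are illustrative because the protocol gives no SAR vs MSO effect. The exact closed procedure is not specified, hence the ranges. The primary tests themselves are unaffected.

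**What to change.** 1. In Table 1, replace 'No' with 'not shown', and report each contrast as an estimate with its CI against the 3-day value.
2. State that an effect of 3 days or more is excluded only when the CI, at the level matching the multiplicity procedure, lies within ±3 days; otherwise call the contrast inconclusive. Say explicitly that exclusion of 3 days is not absence of reactivity or of treatment effect, since smaller effects remain possible.
3. Add a BI-B vs MSO column, a row for neither step significant but BI-B better than MSO (total effect shown, not attributable to either step), and a row for SAR worse than MSO.
4. Change the sentence before Table 1 so that lack of significance is not presented as evidence of absence.
5. Reword the closing advice so that a statement against the intervention rests on the CI for BI-B vs SAR excluding a 3-day benefit, not on non-significance alone.

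The cost is one revised table and two sentences, with no new data and no change to the tests, best settled before results are known. The downside is that some results will be reported as inconclusive.
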